### Interventions

The experimental and control interventions will proceed for six months; an overview of the content of each intervention arm is summarised in Table 1. Each study participant will be allocated to one physiotherapist who will be responsible for their intervention in order to foster the therapist-participant relationship. All therapist-participant interaction will occur through the STAAR app.

**Table 1 Tab1:**
[figure not shown]
Overview of intervention content for the experimental intervention (i-REBOUND programme) and the control intervention across the 6 months period

Black dots represent individual digital sessions between the physiotherapist and study participants. ^a^Prescription of individual exercise programmes and use of self-monitoring of physical activity are optional parts of the experimental intervention, i.e., will be available to study participants who need extra support for exercise and are interested in monitoring their activity

^b^The 2-month follow-up is optional for the control intervention

All physiotherapists will have previous experience of rehabilitation of people post stroke or TIA and of promoting physical activity in people with neurological diseases through the Swedish Physical Activity on Prescription model [16]. Prior to intervention start, the physiotherapists delivering the experimental arm will participate in two 2-h educational sessions delivered by the research team with a focus on theoretical and practical aspects of the i-REBOUND programme (e.g. supervised exercise, self-monitoring and follow ups). The physiotherapists delivering the control arm will receive one 2-h session on theoretical and practical aspects of the control intervention (e.g., individual counselling and follow ups). An introduction to the STAAR digital clinic focussing on communication channels (e.g., video calls) and delivery of core intervention components will be delivered by a representative from the mobile app developers to both experimental and control group physiotherapists. Ongoing support will be provided by the research team to all physiotherapists via bi-monthly meetings (split according to intervention group) to ensure standardisation of intervention delivery.

## Experiment group – mHealth version of the i-REBOUND programme

The experimental intervention derives from the physical activity component of the i-REBOUND programme [33]. This programme seeks to support uptake of physical exercise to improve function and to support long-term engagement in physical activity through behaviour change techniques. The STAAR app will be used for video calls for individual meetings, supervised exercise sessions and follow-ups, and written communication will be enabled through the chat function.

### Physical exercise

The intervention begins with a *start-up meeting with the physiotherapist (week 1)* including an interview based on the participant's medical history and resources (e.g., physical and social) to engage in home-based exercises and physical activity, with discussion of foreseen barriers. Prior to this meeting, instruction videos about the content and goals of the programme, the STAAR app and safety aspects related to home-based exercises will be made available to study participants in the STAAR app. During week 1 of the intervention, a *practice session of supervised exercise* is performed to foster familiarisation of the practical procedures regarding supervised exercise. This includes approximately 10 min of exercise, information about appropriate placement of the smartphone/tablet during training, safety routines regarding balance support, possible need for assistance from relatives, and routines for assessing health status when the participant should refrain from exercising (e.g., feeling unwell).

*Supervised physical exercise sessions (month 1–6).* The targeted dose will be two exercise sessions per week during months 1–3 and one session per week during months 4–6. The training will include supervised exercises individualised to accommodate stroke related or other deficits in strength, balance, and/or coordination and consist of 5 min warm up followed by 20 min of moderate to vigorous intensity exercise performed in 4 blocks of interval training. Perceived exertion will be rated by participants using the Borg Rating of Perceived Exertion Scale before, midway, and immediately after completing the session [40]. During each training block, participants perform intervals alternating between a more demanding and a less demanding exercise (i.e., active rest). Three exercise interval levels will be implemented (Table 2) and exercise examples include marching with knee lift and arm swing, side stepping, rising from a chair, lunges and squats.

**Table 2 Tab2:** Content of supervised physical exercise sessions

		**Intervals**^a^			
**Level**	**Description**	**Duration (sec)**	**Number**	**Number of blocks per session**	**Total dose (min)**
1	­ -Standing and sitting exercises ­ -Emphasis on movement quality and stability	High: 30 Low: 30	5	4	20
2	­ -Only standing exercise ­ -Higher pace and greater movement amplitude compared to level 1	High: 45 Low: 15	5	4	20
3	­ -Only standing exercise ­ -Higher pace, greater movement amplitude and increased movement complexity (e.g., combining arm and leg movements) compared to level 2	High: 60 Low: 15	4	4	20

^a^The intervals include switching between a ‘High’ demanding exercise and a ‘Low’ demanding exercise (i.e., active rest)

The training will initially take place individually with the allocated physiotherapist with introduction to group exercise sessions when deemed suitable by the physiotherapist from a safety and logistical perspective (e.g., schedule conflict), and for those who wish to partake in group exercise. Study participants must participate in at least 2 weeks of individual supervised exercise sessions before taking part in group exercise sessions, in which a maximum of 4 participants with a similar mobility status will be included per group. Participants will have the option to interact with each other verbally through a digital waiting room in the STAAR app prior to and during the group training sessions. Training progression will include utilising three different interval durations of exercise (i.e., shorter active rest, see Table 2) and increasing the exercise's speed and amplitude. The physiotherapists will decide when it is appropriate to progress the exercise based on the study participants’ perceived exertion, the quality of movement with regards to postural stability, and safety during the sessions.

*Individual exercise programme (month 2–6)* will be prescribed as instructional videos in the STAAR app according to participants’ needs to further boost engagement in physical exercise. The type of exercises resemble those performed during the supervised sessions and will be prescribed as either strength exercises (e.g., 15 repetitions × 3 sets) or as a block of aerobic exercise (duration 4–8 min). The individuals performing the exercises in these prescribed videos are people of different ages, gender, and disabilities after stroke (e.g., hemiparesis).

### Behaviour change techniques for physical activity

Two *individual counselling sessions (month 1)* will be performed aimed at assessing motivation, exercise preferences and barriers to physical activity, and inform and initiate individual goal setting regarding physical activity. Prior to the first session (week 1), study participants will complete a digital survey on their expectations of participating in the study, perceived barriers to physical activity, and ability and readiness for behaviour change based on a modified version of Patient Goal Priority Questionnaire [41]. Participants’ responses to the survey will guide the discussion between the physiotherapist and study participants regarding motivation, preferences for, and barriers to, physical activity during the first interview. Educational videos regarding physical activity, aerobic and strength exercises, exercise principles (i.e., specificity and progressive overload), physical activity recommendations according to the World Health Organisation [37], and health benefits of physical activity for secondary stroke prevention and health (e.g., blood pressure reduction, mood, sleep) will be available prior to the first interview and throughout the intervention. The educational videos aim to increase study participants’ awareness and understanding about physical activity, exercise and health. The second interview (week 3 or 4) focuses on defining individual physical activity goals [42, 43] with guidance from the physiotherapist, all of which should be SMART. i.e., Specific, Measurable, Achievable, Realistic and Timely [44].

*Self-monitoring of physical activity*. Participants will be encouraged to monitor their physical activity in the STAAR app using an activity diary. The participant chooses which physical activities they want to monitor and days of the week the activities are planned to be carried out. The opportunity of choice is theorised to support the sense of agency and motivation for physical activity and facilitate the process of behaviour change [21]. The activity diary is intended to provide an overview of the activities monitored in a calendar format (week or month view) with the option to receive push notifications as reminders on performing the activity and feedback on percentage of goal fulfilment over time (i.e., per week or month).

*Structured follow-ups* on goal fulfilment and the need to refine the physical activity goals, including support to overcome barriers, as well as individual home exercises programme refinement will be performed once per month through a video meeting (30 min). Prior to the meeting, study participants will complete a digital questionnaire based on a modified version of Patient Goal Priority Questionnaire [41] on perceived barriers to physical activity, goal fulfilment, capacity to perform the targeted exercise or activities and ability to continue performing these activities in the future. Participants responses to this survey combined with self-monitoring of physical activity will be used to guide the discussion during the structured follow-up.

## Control group—standard approach for physical activity promotion

The control group will receive a programme resembling the Swedish model for ‘Physical Activity on Prescription’ [16] which is often used in clinical practice to promote physical activity in people post stroke or TIA in Sweden. As with the experimental group the control intervention includes two individual counselling sessions (intervention week 1 and 3–4) with the goal to assess motivation, exercise preferences and barriers to physical activity, and to define SMART physical activity goals. Prior to the first session, educational videos on physical activity and health (as per experimental group) will be available to the participants. Three structured follow-ups (months 2, 3 and 6) on goal fulfilment and the potential need to revise the physical activity goals will be undertaken. The interviews, goal setting and follow-ups will be performed as described for the experimental group. The therapist-participant communication will take place through video meetings and chat messages via the STAAR app. Support and feedback from the physiotherapist will be limited to the scheduled follow-ups (i.e., no video or chat communication will be available between the scheduled meetings).

## Data collection

### Feasibility

The feasibility outcomes (i.e., reach, adherence, safety and fidelity) are presented in Table 3 and will be monitored from the study launch (i.e., recruitment) to the last follow-up at 12-months post baseline.

**Table 3 Tab3:** Overview of the feasibility evaluation of the mHealth version of the i-REBOUND programme

Domain	Description	Data collection
***Reach***		
Study recruitment	Proportion of individuals post stroke or TIA screened and deemed eligible for the trial and the proportion of those consenting which are randomised to the trial. Number of study participants requiring assistance to download or access the STAAR app.	Collected by the research team during the recruitment procedures.
Representativeness	Study sample demographics contrasted to national data of the targeted population [13].	Collected by the research team during screening for eligibility and through digital questionnaires administered at baseline.
***Adherence***		
Drop-outs	Number of participants not completing the trial and reasons for withdrawal.	Collected by the research team from point of inclusion until 12-month follow up.
Assessment protocol	Proportion of missing data for clinical outcomes used to assess blood pressure, physical activity, exercise self-efficacy, fatigue, psychosocial wellbeing and health related quality of life.	All clinical outcomes will be self-reported by the participants in the STAAR app at each assessment time point, except for physical activity which will be measured using an activity monitor.
***Safety***		
Adverse events	Number and type of adverse events (including, but not limited to, falls, increase in pain, or hospitalisation).	Reported by either the participants or physiotherapists during the 6-month intervention and recorded by the physiotherapist in the digital clinic.

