**Methods:**

One hundred and twenty participants with stroke or TIA will be recruited via advertisement. A parallel-group feasibility randomised controlled trial design with a 1:1 allocation ratio to 1) i-REBOUND programme receiving physical exercise and support for sustained engagement in physical activity through behavioural change techniques, or 2) behavioural change techniques for physical activity. Both interventions will proceed for six months and be delivered digitally through a mobile app. The feasibility outcomes (i.e., reach, adherence, safety and fidelity) will be monitored throughout the study. Acceptability will be assessed using the Telehealth Usability Questionnaire and further explored through qualitative interviews with a subset of both study participants and the physiotherapists delivering the intervention. Clinical outcomes on preliminary effects of the intervention will include blood pressure, engagement in physical activity, self-perceived exercise self-efficacy, fatigue, depression, anxiety, stress and health-related quality of life and will be measured at baseline and at 3, 6 and 12 months after the baseline assessments.

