### Baseline characteristics

Self-reported demographics (age, sex, comorbidities, level of education, employment status and living situation), date of stroke/TIA, number of previous strokes/TIA, use of mobility device (e.g., walking stick, rollator or wheelchair) and falls history during the previous 6-months will be collected at baseline using digital questionnaires administered through the STAAR app. In addition, self-perceived impact of stroke and lifestyle habits (tobacco, alcohol, physical activity and diet) will be assessed using electronic versions of the Stroke Impact Scale [39] and the screening survey by National Board of Health and Welfare, respectively.

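### Safety is said to be followed to 12 months but adverse events are collected only for 6, and the one described recording route gives the two arms about 43–49 against 4–5 scheduled contacts

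*Protocol article*

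**What the plan says.** **Window.** The Feasibility section under Data collection introduces its outcomes, safety among them: "The feasibility outcomes (i.e., reach, adherence, safety and fidelity) are presented in Table 3". It continues that they "will be monitored from the study launch (i.e., recruitment) to the last follow-up at 12-months post baseline". The abstract agrees: "The feasibility outcomes (i.e., reach, adherence, safety and fidelity) will be monitored throughout the study". In Table 3, however, the data collection entry for adverse events reads "Reported by either the participants or physiotherapists during the 6-month intervention and recorded by the physiotherapist in the digital clinic". The drop-out row of the same table carries a different window: "Collected by the research team from point of inclusion until 12-month follow up".

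**Route.** Participants or physiotherapists may report an event, and the physiotherapist records it. The article describes no other route. Table 4, which lists what both arms complete at baseline and at months 3, 6 and 12, has no adverse event item. The Baseline characteristics section says that "falls history during the previous 6-months will be collected at baseline using digital questionnaires"; no later falls question is described.

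**Contact.** The experimental arm is offered "two exercise sessions per week during months 1–3 and one session per week during months 4–6", together with a start-up meeting, a practice session, two counselling sessions, monthly structured follow-ups and a chat function. The control arm has two counselling sessions and follow-ups at months 2, 3 and 6, the month 2 one being optional (Table 1, footnote b). Outside these, "no video or chat communication will be available between the scheduled meetings".

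**The concern.** Safety is part of the first study objective, and the trial is meant to inform a full-scale one. Two things stand in the way of usable safety data.

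First, the article states two incompatible collection periods. Staff who follow Table 3 would stop recording at month 6. A reader of the abstract or the Feasibility section would expect 12 months.

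Second, the person who records events sees one arm far more often than the other. Table 3 names falls and increased pain among the events, and these often come to light only when someone is in contact with the participant. With equal true rates, more of them would be expected to surface in the experimental arm. A higher count there could then reflect the programme, the contact schedule or both, and the recorded data could not tell these apart. A low control count could likewise be mistaken for a true background rate when the next trial is planned.

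**Working it through.** The article gives no contact total and no adverse event rate, so there is no stated figure to reproduce. The check is a comparison of windows and a count of scheduled contacts.

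**1. Windows**

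| Place in the protocol article | Period for safety or adverse events |
|---|---|
| Abstract, Methods | Whole study |
| Data collection, Feasibility | Recruitment to 12 months after baseline |
| Table 3, Safety row | 6-month intervention |

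Table 3 covers 12 − 6 = 6 months less of follow-up than the other two places. The drop-out row shows that a 12-month window was written into the table where it was wanted, so the 6-month entry cannot be put down to a general shorthand of the table.

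**2. Experimental arm, scheduled contacts over 6 months**

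- Supervised sessions (Physical exercise): 2 per week for one quarter plus 1 per week for the next. With 12-week quarters, 2 × 12 + 1 × 12 = 36. With 13-week quarters, 2 × 13 + 1 × 13 = 39.
- Counselling (Behaviour change techniques): 2.
- Monthly follow-ups: 5 if they run in months 2–6, 6 if they run in months 1–6.
- Start-up meeting: 1, or 0 if combined with the first counselling session.
- Practice session: 1, or 0 if counted among the supervised sessions.

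Minimum: 36 + 2 + 5 + 0 + 0 = 43. Maximum: 39 + 2 + 6 + 1 + 1 = 49. Chat is not counted.

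**3. Control arm**

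2 counselling sessions + 3 follow-ups = 5, or 4 if the optional month 2 meeting is not held. Between the month 3 and month 6 meetings there are none. Over months 4–6 the experimental arm has 12–13 supervised sessions, plus monthly follow-ups.

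**4. Ratio**

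| Experimental contacts | Control 5 | Control 4 |
|---|---|---|
| 43 | 43/5 = 8.6 | 43/4 = 10.75 |
| 49 | 49/5 = 9.8 | 49/4 = 12.25 |

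**5. Sensitivity to attendance (assumed, not in the documents)**

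Suppose only 50–80% of supervised sessions are attended and the other 9 contacts are kept (2 counselling, 5 follow-ups, start-up, practice).

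- Lowest: 0.5 × 36 + 9 = 27, and 27/5 = 5.4.
- Highest: 0.8 × 39 + 9 = 40.2, and 40.2/4 = 10.05.

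The imbalance remains at least fivefold under these assumptions.

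**6. What does not follow.** A contact ratio is not a capture ratio. A hospitalisation may be remembered at the month 3 or month 6 meeting, whereas a minor fall may not. The article gives no capture probability for either arm, so these counts cannot be turned into a biased rate ratio.

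**The case against.** The strongest reply is that the protocol plans no comparison of adverse events. Table 3 evaluates the feasibility of the i-REBOUND programme, the comparative objective lists clinical outcomes only, and the Analysis section treats feasibility outcomes mainly descriptively. For the question of what happens to people who do the programme, close contact is an advantage. This stands, and it limits the point. A reader might infer that a planned between-arm safety test is biased, but no such test is stated.

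Other stronger readings also go too far:

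- **That events can reach the record only through physiotherapist meetings.** Table 3 lets participants report. The research team also uses the digital clinic and sends assessment reminders. The article describes no other route for adverse events, but it does not exclude one. Nor does it say that events are asked about at every session.
- **That the exercise is unsupervised.** The core sessions are supervised by video. Only the optional prescribed programme is done alone.
- **That nothing at all would be known after month 6.** Reasons for withdrawal are collected to 12 months and could reveal some events.
- **That the distortion can be given a number.** Assuming, say, 80% capture against 30–60% yields an apparent ratio of 0.80/0.60 = 1.3 to 0.80/0.30 = 2.7, but those percentages have no basis in the documents.

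It can also be said that the 12-month sentence is a loose umbrella over four domains, since reach and most fidelity items cannot run that long, and that question wording belongs in the full protocol. The first part explains how the mismatch may have arisen, but the sentence names safety and safety can run to 12 months. The second is fair for item wording. It does not cover a conflict between two stated windows, or a recording route and contact schedule that the article itself sets out.

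**Conclusion.** The point holds in two parts. The conflict over the window is certain from the text: safety is promised to 12 months, adverse events are collected for 6, and months 7–12 have no described adverse event capture. The statements must be reconciled.

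The unequal opportunity for capture is a design weakness. The described recorder has 43–49 scheduled contacts with an experimental participant and 4–5 with a control participant, a ratio of 8.6 to 12.25. This counts planned contacts from the text, because the body of Table 1 is not shown. It rests on 12- or 13-week quarters and on whether the start-up and practice sessions are counted separately. Event counts by arm would be confounded with contact frequency. The harm is to the descriptive reading of those counts and to what is carried into the full-scale trial, and its size cannot be derived from the documents.

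**What to change.** 1. Add one identical adverse event item set (falls, increased pain, hospitalisation, other) to the STAAR questionnaires that both arms already receive at months 3, 6 and 12, with answers returned to the research team.
2. Include the baseline falls question in that set. Word it as since the previous questionnaire, so that the month 3 answer does not reach back before randomisation. The recall periods are then 3, 3 and 6 months.
3. Base any description of adverse events by arm on these solicited data. List physiotherapist-recorded events separately, and state that contact differs between arms.
4. Bring the Table 3 window into line with the Feasibility section and the abstract, so that one period is stated throughout.

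The cost is a few questions in questionnaires already scheduled and a small amendment. The drawbacks are slightly longer questionnaires and more reported events in the control arm. The solicited data also depend on return of the questionnaires, so return rates should be shown by arm beside the counts.
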